## **APPROPRIATE PRESCRIBING DEMONSTRATION PROJECT: CLUSTER TRIAL PROTOCOL VERSION 3.0 DATE: 30 May 2016**

### **Background and Rationale**

As part of the 2012 Physicians Services Agreement, the Ministry of Health and Long-Term Care (ministry) and Ontario Medical Association (OMA) established an Appropriate Prescribing Work Group (APWG) tasked to make recommendations to the Physician Services Committee (PSC) on opportunities to improve prescribing in Ontario through voluntary quality-based educational strategies that respect the confidentiality of prescriber practice data. The PSC has approved an initial Demonstration Project of integrated educational strategies starting in Long-Term Care (LTC) homes. The stakeholders decided that appropriate antipsychotic prescribing would be the initial focus of the educational strategies in LTC. This was an appropriate choice as this drug class is known to have substantial risks in the elderly, to be relatively overprescribed given the known risk/benefit ratio, and to be amenable to quality improvement interventions in the LTC setting. The PSC subsequently decided to extend the educational outreach intervention to include falls as a second topic.

#### ***Antipsychotics: evidence for harms***

Antipsychotic medications are typically prescribed in LTC facilities to manage the behavioural and psychological symptoms of dementia (BPSD). However, a significant association has been made between antipsychotic use and increased morbidity and mortality among elderly residents with dementia (Thompson Coon et al., 2014), signalling the pressing need for solutions regarding the appropriate treatment and management of symptoms. Residents are particularly at risk for inappropriate prescribing as they are more fragile, receive interventions from multiple point-of-care staff and are unable to detect errors in their medication. For this reason, residents of LTC facilities may receive up to four times as many prescriptions compared to the elderly in the community (Loganathan, Singh, Franklin, Bottle & Majeed, 2011). The effects of inappropriate prescribing on LTC residents' quality of life are complex: Inappropriate prescribing is often linked to polypharmacy and in turn, adverse drug reactions, causing adverse outcomes, such as increased hospital admissions, increased morbidity and impaired functionality (Beers, 1992; Garcia-Collarte et al., 2014). Specifically, antipsychotic medications are known to be associated with cardiovascular events, parkinsonisms, falls, and death (Rochon, 2007).

#### ***Antipsychotics: evidence of over-use***

Ontario has one of the highest rates in Canada and is known to have one of the highest rates in the world of antipsychotic use. The Canadian Institute for Health Information (2014) reports that 30.5% of LTC residents are inappropriately prescribed antipsychotic medications, without a diagnosis of psychosis. According to a recent report from the Ontario Drug Policy Research Network, in 2012, 38.0% of residents in LTC were dispensed an antipsychotic.

#### ***Antipsychotics: predictors of over-use***

Residents of larger nursing homes are more likely to be prescribed a greater number of inappropriate medications than those in smaller nursing homes (Beers et al., 1992, Ray et al., 1980). Kleijer and colleagues (2014) found that smaller, non-urban LTC facilities with high resident satisfaction report the lowest prevalence of antipsychotic drug use. Similarly, in a study by Hagen and colleagues (2005), it was determined that LTC residents in urban areas received more neuroleptics and benzodiazepines than their LTC counterparts in rural areas (26.1% vs. 15.7%) and 18.0% vs. 7.6% respectively).

Residents having more than one prescriber, having a physician aged 50 years of age or older, or having a non-specialist physician were more likely to be prescribed inappropriate antipsychotic medication (Dhalla et al., 2002). A qualitative analysis of the factors related to psychotropic drug prescription for neuropsychiatric symptoms in LTC residents with dementia revealed important themes (Smeets et al., 2014). Appropriate decision-making, such as “weighing the effectiveness of medications against its side effects and balancing the interests of different stakeholders”, strongly contributed to the prescription of

psychotropic drugs. When providers had limited knowledge of antipsychotic risks and benefits, a greater need for psychotropic drug use among residents was cited. Effective communication and collaboration between professionals in LTC was found to deter or prevent the need for excessive prescription of psychotropic drugs. Lastly, limited personnel to spend enough time with residents, excess employment of temporary nurses, and the employment of nurses with limited people skills, was cited as increasing the need for psychotropic drugs (Smeets et al., 2014).

### ***Antipsychotics: evidence for interventions to reduce prescribing in LTC***

In a systematic review conducted by Thompson Coon and colleagues (2014) on interventions to reduce inappropriate prescribing of antipsychotics among people with dementia in LTC homes, a 12-20% reduction in antipsychotic prescribing levels was found. The type of intervention implemented has an effect on the size of improvements in initiatives targeting antipsychotic improvement in LTC homes. In a systematic review of interventions to optimize prescribing in LTC homes, academic detailing was found as having the strongest evidence for improvements in prescribing, whereas audit and feedback interventions provided small to moderate impact on physician practices (Loganathan et al., 2011). Furthermore, according to Milta and colleagues (2013), educational outreach interventions demonstrate improvements ranging from 18 to 19 percent reductions in antipsychotic use compared to geriatric assessment alone. It has been recommended that in order for educational interventions to be effective at improving inappropriate prescribing, they must be implemented alongside complementary techniques such as academic detailing (Loganathan et al., 2011; Milta et al., 2013). The development of a tracking mechanism that includes specific outcome measures is also recommended (Milta et al., 2013). A randomized control trial in which staff was randomly assigned to receive quarterly audit and feedback plus education about quality improvement demonstrated a decrease in resident falls, behavioural symptoms and pressure ulcers (Rantz et al., 2001).

### ***Addressing the Risk of Falls in Long-Term Care***

Falls are common occurrence among residents in LTC, with approximately 14.8% of Ontario LTC residents and 15.3% of Canadian LTC residents experiencing at least one fall within a 30 day period (CIHI, 2014). Approximately half of all LTC residents will fall at least once per year,

A previous fall triples the risk of future falls (Taylor et al, 2005). A plethora of risk factors have been identified, including age, physical conditions, medications, and behaviour, among others (Balash et al., 2005; Bloch et al., 2011; Dyks and Sadowski, 2015; Tinetti et al., 1992). The majority of these factors are modifiable, presenting an opportunity for the health care team to intervene. A systematic review of interventions to reduce falls in LTC concluded that multifactorial interventions hold more promise (Neyens et al., 2011), which aligns well with the strategy of educational outreach adopted by the APWG.

### **Objectives**

This pragmatic, cluster randomized controlled trial seeks to assess the impact of an intervention that could be readily implemented at scale to improve appropriateness of prescribing. The policy-makers previously determined that all LTC prescribers in the province would be provided with the opportunity to access online practice reports (audit and feedback) that would confidentially describe their prescribing practices for antipsychotic medications, compared to (de-identified) peers. In addition, based on evidence suggesting the potential synergistic effects of audit and feedback with educational outreach (Ivers et al., 2012; Avery et al., 2012), policy makers decided that an educational outreach should be included as part of an ‘Appropriate Prescribing Demonstration Project’.

This proposal forms one part of a program evaluation for the Demonstration Project; given the costs inherent in delivering educational outreach, a rigorous design to assess the added impact of this intervention is desirable. A mixed methods formative evaluation and process evaluation are planned to understand how and why program effects were observed and provide insights regarding scale-up of the interventions.

**Primary question:**

What is the effect of adding educational outreach (AF+EO) compared to the ‘usual’ offering of audit and feedback (AF) and communities of practices on:

1. The prescribing of antipsychotic medications in LTC
2. The rate of falls in LTC

**Secondary questions:**

What is the impact of the interventions on clinical outcomes?

- i. What is the effect of the intervention on acute care utilization (e.g., emergency room) rates?
- ii. What is the effect of the intervention on incidence of patient clinical outcomes and/or adverse effects associated with APMs (e.g., falls, aggressive behaviours)?
- iii. What is the effect of the interventions on medications that might be used as alternatives to APMs (e.g., benzodiazepines)?
- iv. What is the effect of the intervention on medications that increase the risk of falls among residents of long-term care (e.g. benzodiazepines, antihypertensives, opioids, anticholinergics)?

What are the economic implications of the intervention?

- v. What is the cost-benefit when focusing only on prescribing outcomes?
- vi. What is the cost-effectiveness considering all MOHLTC-relevant outcomes?

How and why do the interventions work as observed?

- vi. Was the intervention implemented as desired in LTC homes?
- vii. What were the contextual factors associated with implementation?
- viii. Do the interventions affect precursors of behaviour (e.g., motivation, capability)?

**Design**

Two arm, pragmatic, cluster-randomized trial, with LTC homes allocated to the full, active intervention (featuring educational outreach offered to each prescriber and team members in the home) or standard quality improvement supports (including online audit and feedback reports for each prescriber in the home). The ‘standard’ quality improvement supports represent ‘usual care’ as these are to be launched province-wide; a concurrent control arm with no exposure to a quality improvement intervention is not feasible.

[ClinicalTrials.gov NLM Identifier: NCT02604056]

[figure not shown]

To evaluate the secondary aim of how and why the interventions work as observed, we will employ an embedded single case design with cross case synthesis to gain an in-depth understanding of the conditions and factors associated with implementation of the intervention. The embedded design enables the examination of interactive processes and contextual features through various units of analysis derived from a structured approach to develop programme theory (Davidoff et al., 2015; Portela et al., 2015; Reed et al., 2014). Normalization Process Theory (NPT) and the Consolidated Framework for Implementation Research (CFIR) will be used to guide and structure data collection methods and data analysis. NPT is an established framework for understanding how and whether complex interventions become embedded in health care practice—that is, normalized (Macfarlane et al., 2012). This approach is ideally suited to this study as it entails numerous individuals, professionals, unit, organizational and health systems features that may impact the effectiveness of the audit and feedback intervention in selected LTCs. The CFIR provides a comprehensive taxonomy of defined constructs that are likely to influence implementation (Damschroder et al., 2009). Its application facilitates the identification of active components and further explores the setting in which the intervention is delivered.

### **Eligibility**

LTC homes within pre-determined regions of Ontario are eligible if they express an interest in the full intervention. These regions, or hubs, were chosen because they contain a wide variety of LTC home types within a reasonable travel distance (i.e., <100 km). To be eligible for participation, the medical and administrative leads of the LTC homes must agree to and support the project. Exclusion criteria include: LTC homes with a previous or ongoing involvement in externally supported quality improvement initiatives focusing on antipsychotics; LTC homes without any prescribers caring for at least 10 residents routinely; or LTC homes with fewer than 30 residents. For the topic of antipsychotic medication, we will conduct qualitative interviews in a subset of 3-4 LTC homes that represent the Hamilton geographical hub. The sampling strategies will consist of three variants of purposeful sampling: maximum variation, convenience and snowballing sampling technique. Maximum variation will be used when identifying the LTC homes. The selected homes will represent variations of antipsychotic prescribing rates from high to low. For the topic of falls reduction, we will conduct qualitative interviews in a subset of 5-6 LTC homes that represent the variation that exists within the study sample (e.g. number of beds, urban vs. rural, type of ownership). The sampling strategies will consist of three variants of purposeful sampling: maximum variation, convenience and snowballing sampling technique. Maximum variation will be used when identifying the LTC homes. The selected homes will represent variations among the rate of falls from high to low.

### **Allocation**

Participating LTC homes will be allocated to one of the two arms of the study (active/full intervention versus standard education) using a 2:1 allocation ratio, after stratifying on hub, baseline antipsychotic prescription rates (using published CIHI reports), and size (number of eligible patients). A 2:1 allocation ratio will be used to satisfy the requirements of the sponsor and to improve feasibility of recruitment of homes. LTC homes that share prescribers will be allocated as a unit to avoid contamination. Due to funding restrictions, no more than 38 homes will be allocated to the intensive intervention; if more than 60 homes are recruited, the allocation ratio will be less than 2:1, but the odds of allocation to the full intervention will remain greater than 1:1. Allocation will be conducted by an independent statistician using computer-generated random numbers.

### **Interventions**

### ***Standard quality improvement supports / Usual care:***

Numerous quality improvement initiatives are simultaneously occurring in the LTC sector related to appropriate prescribing, making a randomized comparator all the more important. For instance, CIHI is reporting on antipsychotic use and antipsychotic prescribing has been named a 'priority indicator' for mandatory annual quality improvement plans to be completed by each LTC.

Starting in autumn 2015, in concert with the initiative outlined in this proposal, HQO will be producing confidential **practice reports** using data from ICES to describe selected quality indicators for LTC physicians. This will initially focus on appropriate prescribing of antipsychotics for older men and women with dementia, with an initial focus on how their antipsychotic medication use compares to others in the province plus additional information regarding the clinical and demographic features of their LTC patient roster. Receipt of the reports is voluntary. To receive the reports, physicians must sign up and confirm their identity. They will then receive updated reports quarterly, which they can download from HQO's secure website. In addition, HQO will be launching voluntary, virtual 'communities of practice' to enable sharing of best practices across homes and providers. Starting in autumn 2016, HQO will introduce additional indicators to the practice reports, including benzodiazepines, antihypertensives, and anticholinergic medications.

### ***Active intervention:***

The **educational outreach** program will be delivered by academic detailers, health professionals (often nurses or pharmacists) who have received specific intensive training to support prescribing providers in a particular environment, in this case LTC homes, to make the best or appropriate clinical decisions as possible. It is defined as: "*an innovative method of service-oriented educational outreach for front-line clinicians. It combines the interactive, one-on-one communication approach of industry detailers with the evidence-based, noncommercial information of academia.*" (<http://www.narcad.org/about/aboutad/>)

The intervention requires the Academic Detailers to have direct and ongoing contact with the LTC homes including administrators, providers and staff from the time of launch through to program completion. Given the diverse target audiences that will likely be engaged within the homes, the Academic Detailer will work to understand the context, barriers, capacity, and needs of each home to ensure the service being provided by the detailer is relevant, meaningful and appropriate. The intervention then includes the provision of the following different 'types' of visits made by the Academic Detailer: meetings (likely with administrators to describe the program and value), presentation (large group, inter professional audience), group visit (typically 2-6 providers) and one-on-one visits ('traditional' Academic Detailing visits). In addition, the Academic Detailer provides important service to the LTC homes and providers between visits (i.e., by responding to questions via email or phone) to respond to the needs and build trust/credibility over time.

The Centre for Effective Practice, a Toronto-based non-profit organization retained by the OMA/MOHLTC due to their extensive experience in the area, will manage the educational outreach intervention. Best practices in training of the Academic Detailers and in the components of the program will be applied. Given the nature of the program as a Demonstration Project for the purposes of understanding feasibility in the Ontario context, it is critical to ensure a pragmatic approach to the delivery of the intervention. Therefore, the number of visits per provider or home per topic and the length of visits will not be pre-defined.

### **Data collection**

Outcomes will be assessed using population-level administrative databases linked through unique, encrypted patient identifiers at the Institute for Clinical Evaluative Sciences (ICES). Data will be compiled from the following databases: 1) the Ontario Drug Benefits (ODB) database, covering all prescription medications dispensed to residents in long-term care homes; 2) the Canadian Institute for Health Information (CIHI) databases covering all hospitalizations and emergency department visits; 3) the Ontario Health Insurance Plan (OHIP) database, covering physician billings for procedures and

consultations; 4) the Registered Persons Database covering demographic information including date of death; and 5) the Continuing Care Reporting System (CCRS) database for clinical and demographic information on LTC residents collected using the Resident Assessment Instrument (RAI). Each LTC resident in the province receives a ‘full’ RAI assessment within 2 weeks from admission date, every 12 months from previous full assessment or any other time when the clinical condition of a patient changed considerably and each resident also receives a ‘quarterly’ assessment every 3 months. For each resident, the CCRS database holds demographic and clinical information, including data regarding clinical diagnoses (e.g., dementia, psychosis), dispensing of antipsychotic medications, and occurrences of falls. In addition, a number of validated outcome scales can be derived from the CCRS data, including those related to ADLs, aggressive behaviour, pain, and mood.

The process evaluation involves a mixed-methods approach using individual qualitative interviews and quantitative prescriber surveys.

#### LTC Administrators and Prescribers

We will seek interviews with home administrators, medication prescribers including physicians and nurse practitioners, and consultant pharmacists. A research coordinator will inform participants of the nature of the study being to understand how stakeholders respond to and interact with the interventions and also to explore for any unintended consequences—exploring their experiences associated with the implementation of the academic detailing intervention.

#### Academic Detailers

All academic detailers will be invited to participate in interviews. A research coordinator will inform the academic detailers of the nature of the study - exploring their experiences associated with the implementation of the academic detailing intervention.

#### Interview Guides

Written consent will be obtained prior to the interviews (see attached Interview Consent Forms). The interviews will be guided by the detailed program theory (which itself will be refined iteratively), the CFIR, and NPT (Damsroder et al., 2009; MacFarlane et al., 2012; Portela et al, 2015) (see Administrator & HCP Interview Guide). The interview guides will be pilot tested prior to their full-scale use. Participants will be informed that participation in the interview of the study is voluntary and they can withdraw from the study at any time without penalty to their employment. It is expected interviews will last between 30 to 60 minute interviews. Participants will also be informed that they can skip questions during the interview without affecting their participation in the study and that interviews will be digitally audio taped and transcribed verbatim.

#### Prescriber Survey

To understand the intervention’s mechanism of change, we will survey participating clinicians and LTC administrators in both groups prior to intervention delivery and again 6 months later to measure theoretical constructs targeted by our intervention and changes in these constructs associated with the intervention (Grimshaw et al., 2007). We will assess constructs based on the COM-B model (capability, opportunity, and motivation) (Michie et al., 2011), which are specifically targeted by the intervention. These constructs will be assessed for each of the targeted clinical behaviours. Questions will include validated items from the Determinants of Implementation Behaviour Questionnaire (Huijg et al., 2014) as well as measurements of self-efficacy and coping planning, two factors which have been shown to influence clinician behaviour (Presseau et al., 2014).

### **Outcomes**

The following primary and secondary prescribing and clinical outcomes will be assessed in the trial:

| Variable        | Definition | Source |
|-----------------|------------|--------|
| Primary outcome |            |        |

|                                                   |                                                                                       |                   |
|---------------------------------------------------|---------------------------------------------------------------------------------------|-------------------|
| Antipsychotic dispensing                          | Number of days with antipsychotic prescriptions in the last week (count, range 0 – 7) | RAI               |
| Secondary prescribing outcomes             |                                                                                       |                   |
| Antipsychotic prescribing                         | Any antipsychotic Rx during the past month (dichotomous)                              | ODB               |
| Mean Antipsychotic dose                           | Dose equivalent of antipsychotic dispensed in the past month (continuous)             | ODB               |
| Benzodiazepine (or z-drug) prescribing            | Any Rx during the past month (dichotomous)                                            | ODB               |
| Anti-depressant prescribing                       | Any Rx during the past month (dichotomous)                                            | ODB               |
| Acetaminophen prescribing                         | Any Rx during the past month (dichotomous)                                            | ODB               |
| Secondary clinical outcomes                |                                                                                       |                   |
| Difficulty in performing activities               | ADL long form scale (continuous variable, range 0-28)                                 | RAI (ADL_long_cc) |
| Aggressive behaviour scale                        | Extent of aggressive behaviour (continuous variable, range 0-12)                      | RAI (ABS_cc)      |
| Pain                                              | Pain scale (continuous variable, range 0-3)                                           | RAI (PAIN_cc)     |
| Depression                                        | Depression rating scale (continuous variable, range 0-14)                             | RAI (DRS_cc)      |
| Falls                                             | Number of falls in the past month (count)                                             | RAI (J4: a)       |
| Secondary health care utilization outcomes |                                                                                       |                   |
| ER visits                                         | Number of ER visits during the previous 6 months (count)                              | CIHI/NACRS        |
| Hospitalizations                                  | Number of hospital visits visit during the previous 6 months (count)                  | CIHI              |

All **primary and secondary prescribing outcomes** will be assessed at baseline (pre-intervention) and at 3 and 6 months post-intervention. Here, "baseline" is defined as the week or month immediately prior to randomization, while post-intervention measurements are defined as the third and sixth months after randomization. These outcomes will be assessed on all residents who are alive at the time of the assessment and who were present in the home for the full duration of the prior week/month.

All **clinical outcomes** (e.g., ADL, behaviour scale, depression, falls) will be assessed at baseline and at 3 and 6 months post-intervention. The most current data collected immediately prior to the implementation of the intervention, and at each post-randomization time point will be used, regardless of mortality status at the subsequent time point.

All **health care utilization outcomes** (number of ER visits and hospitalizations during the previous 6 months) will be assessed at baseline and at 6 months post-intervention. A longer duration is required to allow adequate time for the intervention to have an effect on these outcomes. All residents present in the homes at any time during the study will contribute to the analysis using person-time of follow-up. As the EO intervention may be rolled out over a 2-3 month period due to logistical restraints, homes allocated to the control arm will have their measurement times assigned randomly from the assessment times of the intervention homes in the same stratum.

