### **Analysis**

Descriptive statistics will be calculated for all variables of interest: continuous variables with a normal distribution will be described using means and standard deviations (medians and inter-quartile ranges in the case of skewed distributions), whereas categorical variables will be summarized using frequencies and proportions. All analyses will be by Intention To Treat. Analyses will be conducted using SAS v.9.3 and statistical significance will be assessed at the 5% level.

The **primary outcome** describing **dispensing of medication** (number of days with antipsychotic/benzodiazepine/antihypertensive/anticholinergic prescriptions in the last week) will be analyzed using generalized linear mixed effects regression with multinomial distribution and cumulative logit link. To account for the staggered implementation of the intervention, phase (phase1/phase2) will be included as a fixed effect. Random intercepts and slopes will be specified to account for intracluster

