**Secondary clinical outcomes** measured as continuous variables (e.g., ADL, depression score) will be analyzed using linear mixed effects regression with normal distribution and identity link. Fixed and random effects will be specified as described for the prescribing outcomes. The effect of the intervention will be expressed as adjusted least square mean differences with 95% CI. Secondary clinical outcomes measured on an ordinal scale (e.g., pain scale) at baseline, 3 months and 6 months will be analyzed using generalized mixed effects regression as described for the primary outcome but using multinomial distribution and cumulative logit link. Presence of any falls in the past 30 days will be analyzed at baseline, 3 months, and 6 months using generalized linear mixed effects regression with binomial distribution and logit link, as described for the primary outcome. In the Intent-To-Treat analyses for the secondary clinical outcomes (e.g., ADL, falls, pain), the potential effect on inferences of patients who died will be examined using sensitivity analyses under conservative assumptions: for example, patients who died during the interval will be assigned the worst possible score. Depending on the extent of patient turnover within homes, additional analyses for primary and secondary outcomes will explore inclusion of subject-specific random effects to account for repeated measures on the same patient over time (i.e., a cohort rather than cross-sectional design).

**Health care utilization outcomes** (number of ER visits and hospital visits) will be analyzed at 6 months using generalized linear mixed-effects regression with Poisson or negative binomial distribution and log-link, with log person-time of follow-up as an offset term. The following fixed effects will be included: intervention, phase, and stratification variables, as well as the rate of health care utilization at the home 6 months prior to the intervention. Patient covariates will be adjusted for as specified for the primary outcome. Home will be included as a random effect. The effect of the intervention will be expressed as adjusted Rate Ratio (RR) with 95% CI.

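### Falls is defined as a monthly count but analysed only as any fall in 30 days; the two must be reconciled because falls is named in a primary question

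*Protocol*

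**What the plan says.** Falls appears in three forms in the protocol.

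- **Primary question, item 2:** the effect of adding educational outreach on "The rate of falls in LTC".
- **Outcomes table, under secondary clinical outcomes:** "Number of falls in the past month (count", source RAI item J4:a.
- **Analysis, secondary clinical outcomes:** "Presence of any falls in the past 30 days will be analyzed at baseline, 3 months, and 6 months", by "generalized linear mixed effects regression with binomial distribution and logit link, as described for the primary outcome".

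The Analysis section also contains a count model, "Poisson or negative binomial distribution and log-link, with log person-time of follow-up as an offset term", but applies it only to ER and hospital visits. No count or rate model is given for falls.

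The background section on falls gives one 30-day figure for Ontario: 14.8% of residents "experiencing at least one fall within a 30 day period". It also states that "A previous fall triples the risk of future falls".

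**The concern.** A variable defined as a number of events is modelled as present or absent, and nothing in the protocol says that it will be dichotomised or why. This is not detail left for a later analysis plan: the protocol fixes both the definition and the model, and they differ.

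Two things are at stake. First, the target of a primary question is left open between a rate ratio for falls and an odds ratio for being a faller, so an analyst could support either from the text after seeing the data. Second, if the source item holds a number, yes/no coding ignores every fall after the first in the window. A resident who goes from four falls to one is coded the same both times. The protocol's own remark on recurrence makes repeat falls relevant to a falls-prevention programme.

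**Working it through.** **Step 1. Compare the entries.** The Outcomes table marks variables as dichotomous where they are so, for example any antipsychotic prescription in the past month. Falls is marked as a count, as are ER visits and hospitalizations. Those two receive a Poisson or negative binomial model and a rate ratio; falls receives a logit model. No other section reconciles this.

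**Step 2. Is there a falls figure to reproduce?** No. The Power section covers the antipsychotic outcomes only. What follows is an illustration, and it applies only if J4:a records a number.

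**Step 3. Mean falls per resident-month, m, given P(any fall) = 0.148**, so P(no fall) = 0.852. The dispersion values d are assumptions; the protocol gives none.

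- Poisson: m = −ln(0.852) = 0.160.
- Negative binomial: solve (1 + d·m)^(−1/d) = 0.852, so m = (0.852^(−d) − 1)/d.

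**Step 4. Share of falls that are second or later falls in the window.** Each faller contributes one first fall, so the share is 1 − 0.148/m.

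**Step 5. Effect confined to repeat falls.** Halve the repeat falls and leave the proportion of fallers at 14.8%. The any-fall odds ratio stays at 1.00 by construction. The falls rate ratio is 1 − share/2.

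**Step 6. General reduction.** Multiply m by 0.75 at every level, recompute P(any fall), and compare its odds with 0.148/0.852 = 0.174.

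| Model | m | Repeat share | Rate ratio, repeat falls halved | Any fall after rate ratio 0.75 | Any-fall odds ratio |
|---|---|---|---|---|---|
| Poisson | 0.160 | 7.6% | 0.96 | 11.3% | 0.73 |
| d = 1 | 0.174 | 14.8% | 0.93 | 11.5% | 0.75 |
| d = 2 | 0.189 | 21.6% | 0.89 | 11.7% | 0.76 |
| d = 3 | 0.206 | 28.0% | 0.86 | 11.9% | 0.78 |

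Worked line for d = 3: 0.852^(−3) = 1.617, so m = 0.617/3 = 0.206 and the share is 1 − 0.148/0.206 = 28.0% (unrounded m). With m × 0.75 = 0.154, P(no fall) = (1 + 3 × 0.154)^(−1/3) = 0.881, so any fall is 11.9%, with odds 0.135 and odds ratio 0.135/0.174 = 0.78.

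The yes/no analysis would therefore miss an effect confined to repeat falls, but it would pick up a general one.

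**The case against.** The strongest reply is that the table entry is simply loose and the rest of the protocol is coherent. Three points support it.

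- **Use of the word rate.** The protocol often uses it for a proportion of residents: the section on antipsychotic over-use supports its talk of rates with 30.5% and 38.0% of residents, and Eligibility, Allocation and Recruitment speak of prescribing rates in the same way. The background gives falls as the percentage with at least one fall in 30 days, which is exactly the variable and window analysed. The background, the primary question and the analysis can thus be read as agreeing. A reader might infer that the primary falls question goes unanswered; the documents do not establish that.
- **The source item.** A reader might also infer that a recorded count is being thrown away. Data collection says only that the database holds occurrences of falls, and nothing shows that J4:a records a number. If it is yes/no, there is no count to lose.
- **Table labels elsewhere.** Antipsychotic days are labelled a count and pain a continuous variable, yet both are analysed as ordinal.

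All three points stand, and they narrow the consequence. They do not remove the conflict. Falls is not merely given a type label: the entry itself defines the outcome as a number of falls, and the analysis uses a different variable. If the benign reading is right, the table is wrong and needs correcting.

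**Conclusion.** The point holds in this form: the definition of falls in the Outcomes table and the only falls analysis disagree, and the wording of the primary question does not settle which is meant. That rests on the text alone and is firm.

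The loss of information is conditional. It arises only if J4:a records a number, and then only for repeat falls within one 30-day window. Its size runs from about 8% of falls (Poisson) to 15% to 28% (assumed dispersion 1 to 3). The analysis is not blind to a falls effect: a uniform 25% fall in the rate would appear as an any-fall odds ratio of about 0.73 to 0.78 under the same assumptions. That estimate would still be an odds ratio for being a faller and should not be presented as an effect on a fall rate.

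The correction is worth making because falls is named in a primary question. It does not touch the antipsychotic primary outcome.

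**What to change.** First confirm what RAI item J4:a records, and settle the matter before outcome data are examined.

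- **If it is yes/no:** restate the outcome in the table as any fall in the past 30 days (dichotomous), word the primary question as the proportion of residents who fall, and report the odds ratio as such.
- **If it is a number:** keep the count. Analyse it with a negative binomial (or Poisson) log-link mixed model at baseline, 3 and 6 months, with the same fixed and random effects as the other repeated outcomes. Report a rate ratio, and keep the any-fall model as supportive.

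The ER-visit model cannot be lifted unchanged. It is a single 6-month analysis with a person-time offset and the home's prior 6-month rate as a covariate, so it must be adapted to repeated 30-day look-backs.

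The cost is protocol wording and at most one additional model, with no new data.
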